### End of participation in the study

A patient will leave the study if he (she) refuses to participate to it, if an exclusion criterion appears during hospital stay, if a severe adverse event occurs or if there is an allergy to one of the antiseptic agents.

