### Patients

All consecutive adult patients aged over 18 years, hospitalized in one of participating ICUs for an expected length of stay of >2 days and requiring insertion of at least one peripheral arterial catheter and/or a non-tunneled central venous catheter and/or a hemodialysis catheter and/or an arterial pulmonary catheter will be included in the trial. Exclusion criteria will be catheters inserted outside the ICUs, patients with a history of allergy to any of the antiseptic agents studied, patients likely to die within 48 h after admission, and use of catheters coated with antimicrobial agents.

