### Assessment endpoints

Density incidence of major catheter-related infection, catheter colonization, catheter-related bloodstream infection, and skin colonization at catheter insertion site for all catheters and for arterial or central venous catheters only; mortality rate in ICU and in the hospital; length of stay in ICU and in hospital; incidence of cutaneous allergy using the International Contact Dermatitis Research Group scale [17]; cost of each strategy of skin preparation.

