### Statistical analysis

The data will be analyzed blindly with regard to treatment arms. An intention-to-treat analysis is scheduled, and it will include all patients except those with no catheter inserted and those who will have withdrawn their consent to participate in the study. No interim analyses are planned. Demographic data will be described in number and percentage or median and interquartile range for quantitative and qualitative variables and compared with χ^2^ test or Mann–Whitney, as appropriate. Kaplan-Meir curves of the risks of major-CRI and CR-BSI and catheter colonization will be plotted for each treatment group. Proportional hazard assumption will be assessed by plotting Schoenfield’s residuals with time.

Analysis of antiseptic efficacy will be carried out using a marginal Cox model stratified by centers [18]. This model takes into account the censored nature of the data and also accounts for intra-cluster (intra-patient) dependence (more than one catheter per patient) using a robust sandwich covariance matrix. The interaction between scrubbing and antiseptic effect will be sought first by forcing the interaction term in the final model. In the absence of interaction, analysis of skin scrubbing and chlorhexidine effects will be performed independently. For secondary endpoints the analyses will not be controlled for multiple testing.

Comparisons of skin cultures between groups will be assessed through multiple factor ANOVA (Center, scrubbing, antiseptic).

Analyses will be done using SAS 9.x (SAS Institute, Cary, NC,USA) and R (R foundation, Vienna, Austria) softwares.

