### Length of patient follow-up

Patients will be followed up for the duration of their stay in ICU. Insofar as possible the catheter will be removed before patients’ discharge from ICU. If not, one peripheral and one through-the-line blood culture will be drawn at discharge and a visit at day 3 will take place in order to enquire about the diagnostic of catheter-related infection.

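### The exit rule ends participation after three post-randomization events that the intention-to-treat definition does not exempt, so later outcomes go uncollected and the censoring may be informative

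*Protocol article*

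**What the plan says.** All references are to the protocol article, Methods.

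- **End of participation in the study.** It opens with "A patient will leave the study if he (she) refuses to participate to it". It then adds three further grounds: an exclusion criterion that appears in hospital, and "if a severe adverse event occurs or if there is an allergy to one of the antiseptic agents".
- **Statistical analysis.** The analysis is by intention-to-treat: "it will include all patients except those with no catheter inserted and those who will have withdrawn their consent to participate in the study". Antiseptic efficacy is tested with a marginal Cox model stratified by center, with a robust sandwich variance for several catheters in one patient.
- **Length of patient follow-up.** "Patients will be followed up for the duration of their stay in ICU", with a day 3 visit for patients discharged from the ICU with the catheter in place.
- **Assessment endpoints.** Besides infection, colonization and cutaneous allergy, the list has "mortality rate in ICU and in the hospital; length of stay in ICU and in hospital".
- **Study design.** Nurses and physicians know which antiseptic is used. The microbiologists and the adjudication committee do not.

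**The concern.** Leaving a treatment and leaving a trial are different events, and the article treats them as one. Intention-to-treat needs outcomes to be recorded after a patient stops the assigned strategy, and the exit rule read literally stops the recording. Patients are expected to have at least two catheters on average, so an exit around the first can remove all information on the next.

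The triggers arise after randomization and are not neutral. Allergy is tied to the agent received. A severe adverse event is tied to prognosis. Both are recognized by staff who know the arm. If those who exit would have had a different later infection hazard from those who stay, and this differs between arms, the antiseptic comparison is biased. Mortality and length of stay would also be missing for a group selected on being unwell.

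**Working it through.** **1. Exit reasons against the permitted exclusions.**

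| Reason for leaving | Exempt from intention-to-treat? | Can it depend on arm or prognosis? |
|---|---|---|
| Refusal | Yes, as withdrawn consent | Possibly, but data collection cannot be required |
| Emerging exclusion criterion | No | Mostly a catheter feature (outside the ICU, coated); no evident link to arm, except a new allergy |
| Severe adverse event | No | Prognosis; recognized by unblinded staff |
| Allergy to an antiseptic | No | Arm |

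Three of the four reasons have no counterpart in the analysis definition. All three cut short the follow-up that is promised for the ICU stay. No section says that data continue to be recorded after exit.

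**2. What is lost and what is not.** The article does not say that data before exit are deleted, so a patient can stay in the randomized arm, censored at exit. The event that triggers the exit has itself been seen. What is lost is everything afterwards. A catheter still in place at exit adds a complication. Under Definitions, a catheter that is not cultured counts as not colonized unless there was otherwise unexplained sepsis. If such a catheter is kept in the analysis without a culture, it may be scored as a non-event for colonization.

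**3. Numbers are not the problem.** The plan's own figure reproduces. For 5% versus 2.5%, two-sided 5%, 80% power and pooled variance:

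n = [1.960 × √(2 × 0.0375 × 0.9625) + 0.842 × √(0.05 × 0.95 + 0.025 × 0.975)]² / 0.025² = 906 catheters; 906 / 2 = 453 patients per arm, as stated.

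The planned 2,400 patients give 1,200 per antiseptic. The 6% allowance is 0.06 × 2,400 = 144 patients. Even with a 20% loss (assumed), power is 98.3% if catheters are treated as independent and 82.3% if each patient counts as one unit. The allowance covers numbers only and does nothing about selective loss.

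**4. When censoring at exit biases the hazard ratio.** Suppose a share s of an arm's time at risk lies after exit, at k times the hazard of the remaining time. With full follow-up the arm's average rate is proportional to D = 1 − s + s·k. After censoring it is proportional to 1. With a true ratio of 0.50, to a rate approximation:

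observed ratio = 0.50 × D(povidone iodine) / D(chlorhexidine).

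- If k = 1, D = 1 and the ratio stays at 0.50 however unequal the exits are.
- If s and k are the same in both arms, the two D cancel and the ratio again stays at 0.50.
- If s = 0.15 and k = 2 in one arm only (assumed), D = 0.85 + 0.30 = 1.15. The ratio is 0.50 × 1.15 = 0.58 with exits in the povidone iodine arm, or 0.50 / 1.15 = 0.43 with exits in the chlorhexidine arm.
- If k is below 1, each shift reverses.

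The article gives neither s nor k for either arm. The example shows the mechanism and estimates nothing.

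**5. Does the planned model repair it?** No. Cox regression needs censoring to be non-informative given the terms in the model. The sandwich variance addresses correlation within patients, and stratification addresses center. Neither acts on selective exit.

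**6. Hospital endpoints.** Stated follow-up ends at ICU discharge, or at day 3 after it if a catheter remains. Deaths and stays that end in the ICU are seen. For patients still in hospital after that point, hospital mortality and hospital length of stay lie beyond the stated follow-up.

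**The case against.** The strongest reply is that the two sections can both be true. The analysis section says which patients are included and does not promise complete outcomes, and the Cox model is built for censoring. Blinded cultures and adjudication also limit bias in classifying events. An article is a condensed text, and the full protocol may define a severe adverse event and its handling. All of this stands against stronger readings, but it does not remove the point. The article states outright that such patients leave the study and that follow-up covers the ICU stay. Blinded assessment cannot recover outcomes that nobody records.

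Four stronger readings are tempting and are not supported:

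- **A numerical bias range.** One might remove 10% to 20% of events from one arm and get 0.50 × 0.90 = 0.45 to 0.50 × 0.80 = 0.40, or 0.50 / 0.90 = 0.56 to 0.50 / 0.80 = 0.63. That is risk-ratio arithmetic with intact denominators, whereas censoring also removes time at risk. In the example above, 0.30 / 1.15 = 26% of the arm's events are lost. Counting events alone gives 0.50 × 0.74 = 0.37 or 0.50 / 0.74 = 0.68, against 0.43 or 0.58 on the rate scale. The shares are assumptions in any case.
- **The analysis is no longer intention-to-treat.** Patients may remain in their arm, censored at exit.
- **Cutaneous tolerance, or the primary event, is lost.** An allergy or infection that triggers the exit is observed at that moment. Only later catheters and later events are affected.
- **The hospital endpoints are not observed at all.** Routine records could supply them. The patient-level list under Data collection does not name ICU mortality or ICU length of stay either, so it is plainly not exhaustive.

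**Conclusion.** The conflict holds. Three exit grounds that arise after randomization end participation, the intention-to-treat definition does not exempt them, and the promised follow-up is cut short. Outcomes after exit are not collected under the text as written. The resulting censoring may be informative, because staff are unblinded and the triggers can depend on arm or prognosis, and the planned model does not correct it. This rests on reading the exit rule literally and on no unseen text keeping data collection open.

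The size and direction of any bias cannot be given from this document. Power is not the issue. The gap between the stated follow-up and the hospital endpoints is secondary and is a matter of alignment.

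**What to change.** Reconcile End of participation in the study, Statistical analysis and Length of patient follow-up along these lines:

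- Separate leaving the assigned antiseptic strategy from ending data collection. The first is a clinical decision, which this point leaves as it is.
- State that only refusal or withdrawal of consent ends data collection.
- After any other trigger, keep recording the routine catheter, culture, infection, length-of-stay and survival data, and analyze all catheters in the randomized arm.
- Report the number, reason and timing of exits from the assigned strategy by arm.
- Record vital status and date at hospital discharge from routine records, so that follow-up reaches the hospital endpoints.

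The cost is one amendment and a few more routine data items for patients who would otherwise have exited, with no new procedures. With 691 of 2,400 patients included at the time of the article, 2,400 − 691 = 1,709 were still to come. Data not recorded after an exit may be impossible to recover at analysis.

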## Discussion

This study will help to update recommendations on how to prepare the skin prior to insertion of a vascular catheter and, by extension, an epidural catheter, of which it is estimated that approximately 30 million are inserted every year in France. Although chlorhexidine is considered the most effective antiseptic in reducing catheter-related infections, its superiority over alcoholic povidone iodine is based on only a few studies, which have not included enough patients to demonstrate any significant effect on infection. A study adequately powered to demonstrate the superiority of chlorhexidine over alcoholic povidone iodine in reducing major catheter-related infections is warranted (7). Skin scrubbing is rapid (<2 min) and inexpensive (<€1), but since it is performed several million times a year by nurses in French hospitals, it leads to substantial costs.

Study limitations. The possible impact on the findings of different types and concentrations of alcohol contained in both antiseptics studied, of different methods of application of antiseptics and of different antiseptics used for manipulating the lines and of three-way taps shall not be assessed. However, antiseptics will be used in their available formulations and in accordance with the manufacturers’ recommendations.

### Trial status

The trial is currently including patients. The inclusion process started on 26 October 2012 and the number of patients included is 691. The estimated length of inclusion time is 15 months.

## Abbreviations

CDC: Centers for Disease Control and Prevention; CFU: Colony forming unit; CI: Confidence interval; ICUs: Intensive care units; RR: Relative risk; SAPS: Simplified acute physiology score; SF2H: French Society of Hospital Hygiene; SIRS: Systemic inflammatory response syndrome; SOFA: Sequential organ failure assessment.
